#### Analysis of clinical data

All statistical analyses will be conducted using SPSS version 26.0. Continuous variables will be presented as means ± standard deviations or medians (interquartile ranges), depending on distribution, and compared using independent samples t-tests or Mann-Whitney U tests, as appropriate. Categorical variables will be expressed as frequencies (%) and analyzed using Chi-square or Fisher’s exact tests. A repeated-measures analysis of variance (ANOVA) will be applied to evaluate longitudinal changes in each outcome, with group (active vs sham) as the between-subject factor and time (baseline, post-intervention, follow-up) as the within-subject factor. If the assumption of sphericity is violated according to Mauchly’s test, the Greenhouse-Geisser correction will be applied. Significant interactions will be followed by Bonferroni-adjusted simple-effects comparisons to determine between-group differences at each time point and within-group changes across time.

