### Study outcomes

#### Primary outcome

The primary outcome is to compare the response rate of depressive symptoms between the active stimulation group and the sham stimulation group after intervention. The response rate is defined as a reduction of 50% or more in the HAMD-17 score compared with the baseline. Remission is defined as a HAMD-17 score of ≤ 7 (32).

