### Statistical analysis

#### Sample size

The sample size for this exploratory trial was determined *a priori* using G*Power software (version 3.1). An F-test was employed based on an effect size (Cohen’s d) of 0.38 by Chu et al. (2021). A total of 50 participants were required to achieve 80% statistical power at a two-sided alpha level of 0.05 (37). Anticipating an approximate dropout rate of 10%, the planned enrollment was at 56 participants.

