### Data management

Study data will be recorded in the Case Report Form (CRF) in a timely, comprehensive, and accurate manner. Two researchers will separately enter the data into EpiData software (Version 3.1, developed by JM Lauritsen of the EpiData Association) (40). Subsequently, the built-in double-check function of the software will be used to verify the entered data, ensuring data accuracy. All study-related electronic files will only be accessible to authorized personnel, and computer systems will adopt password protection measures to ensure data security. To ensure the consistency of study-related documents, each participant will be assigned a unique identification number upon enrollment. Paper-based CRFs and study documents will be stored in a designated secure office area, managed by the study coordinator, and properly kept in a locked security cabinet.

Researchers must strictly adhere to the study protocol, conduct timely verification, collection, recording, and protection of data, and minimize the possibility of data loss. If data are missing for a small number of patients, multiple imputation will be used for processing. Meanwhile, source data verification will be conducted by comparing registered data with original medical records to assess the accuracy, completeness, and representativeness of the registered data.

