### Discontinuation of assigned intervention

Participants may withdraw from the study at any time without penalty. The following discontinuation criteria apply throughout the entire study period. The Principal Investigator may discontinue the assigned intervention if any of the following occur:

Seizure or other acute neurological event.Emergent mania meeting DSM-5 criteria.New-onset psychotic symptoms.Persistent non-adherence to study procedures.Illicit substance use or a positive urine toxicology test.

Participants discontinued from the intervention will continue to receive standard clinical care, and their safety will be monitored until symptoms resolve or stabilize.

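### For the continuous scales, baseline as a visit level plus an interaction gate loses power that a baseline-adjusted T1 comparison would recover; one analysis of response should be named as primary

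*Protocol article*

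**What the plan says.** Under Analysis of clinical data, the article gives three routes.

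- Continuous variables are compared by t-test or Mann-Whitney test.
- For categorical variables: "Categorical variables will be expressed as frequencies (%) and analyzed using Chi-square or Fisher’s exact tests".
- For change over time: "A repeated-measures analysis of variance (ANOVA) will be applied to evaluate longitudinal changes in each outcome", with group as the between-subject factor and "time (baseline, post-intervention, follow-up) as the within-subject factor". The follow-up rule is: "Significant interactions will be followed by Bonferroni-adjusted simple-effects comparisons to determine between-group differences at each time point".

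No analysis adjusts for the baseline score, and no route is labelled primary. Under Primary outcome, the endpoint is binary: "The response rate is defined as a reduction of 50% or more in the HAMD-17 score compared with the baseline". Under Data management: "If data are missing for a small number of patients, multiple imputation will be used for processing". Table 1 marks the clinical scales at four visits and P300 at two (Day 0 and Day 10).

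**The concern.** When baseline is a level of the time factor, the treatment effect sits in the group-by-time interaction. That test spreads its power over several degrees of freedom (three with four visits). The T1 difference is then examined only if the interaction is significant, and by a comparison that ignores each patient's baseline score. A real T1 effect can fail at either step. An analysis that adjusts for baseline and tests T1 directly needs one test and has less residual variance. With about 25 analysable patients per arm, that efficiency matters.

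Two wording problems go with this. "Each outcome" cannot include response, which is defined relative to baseline and so has no baseline value. And because the section offers several routes without naming a primary one, the analysis that decides response at T1 is not fixed.

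**Working it through.** **The plan's sample size.** The article gives an "effect size (Cohen’s d) of 0.38" and N = 50 for 80% power at two-sided 0.05. For two groups, n per arm = 2(1.960 + 0.842)²/d². At d = 0.38 this is 2 × 7.849/0.1444 = 108.7, so 109 per arm and 218 in total (220 by the F-test). N = 50 is not reproduced. If 0.38 is Cohen's f, d = 2f = 0.76 and n = 2 × 7.849/0.5776 = 27.2, so 28 per arm and 56 in total (58 by the F-test), which is nearer. The step to 56 does reproduce: 50/0.9 = 55.6. The sample size is a separate matter. It is used here only to justify showing both effect sizes.

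**Inputs.** From the article: 25 per arm (50 in total, 1:1), four visits for the clinical scales, two-sided 0.05. Assumed: unit SD, equal correlation ρ between visits (0.5, range 0.3 to 0.7), no effect at baseline and effect d at T1, T2 and T3.

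**Interaction test.** Noncentrality λ = (n/2) Σ(δⱼ − δ̄)²/(1 − ρ). With effects (0, d, d, d) the sum is 3(d/4)² + (3d/4)² = 0.75d². At ρ = 0.5:

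- d = 0.38: λ = 12.5 × 0.75 × 0.1444/0.5 = 2.71
- d = 0.76: λ = 12.5 × 0.75 × 0.5776/0.5 = 10.83

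**T1 comparison, normal approximation.** Power = Φ(d√(n/2) − 1.96). ANCOVA replaces d by d/√(1 − ρ²).

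- d = 0.38, unadjusted: Φ(1.344 − 1.96) = 27%. Adjusted: 0.38/0.866 = 0.439, Φ(1.551 − 1.96) = 34%.
- d = 0.76, unadjusted: Φ(2.687 − 1.96) = 77%. Adjusted: 0.878, Φ(3.103 − 1.96) = 87%.

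**Simulation.** The two-step route needs simulation: 20,000 trials per row, Greenhouse-Geisser-corrected interaction. "Gated" means interaction significant and baseline-unadjusted T1 difference significant at 0.05.

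| d | ρ | Interaction alone | Gated T1 | Ungated t-test, T1 | ANCOVA, T1 |
|---|---|---|---|---|---|
| 0.38 | 0.3 | 18% | 7% | 26% | 28% |
| 0.38 | 0.5 | 23% | 8% | 26% | 33% |
| 0.38 | 0.7 | 38% | 12% | 26% | 45% |
| 0.76 | 0.3 | 61% | 48% | 75% | 78% |
| 0.76 | 0.5 | 78% | 60% | 75% | 85% |
| 0.76 | 0.7 | 95% | 72% | 75% | 95% |

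Smaller runs (5,000 to 6,000 trials) differ by about one point. The gated column favours the plan, because it omits the Bonferroni step. With Bonferroni over four visits (0.0125), the ρ = 0.5 figures fall to 4% and 44%. If the 0.76 effect halves at each follow-up (1, 0.5, 0.25), ρ = 0.5 gives 53% gated against 85% for ANCOVA.

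**The case against.** Much of the case on the other side stands.

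- **The primary is not behind the gate.** A reader might infer that the binary primary has no fitting test. The section assigns chi-square or Fisher tests to categorical variables, so it does, and that test depends on no interaction. The power figures above concern continuous scores and say nothing about response.
- **The gate may not be the only route.** The section also lists t-tests for continuous variables and does not confine them to baseline. Against an ungated T1 t-test the gain is modest: 33% against 26%, or 85% against 75%, at ρ = 0.5.
- **The interaction test is not always the weaker one.** At d = 0.76, constant effect and ρ = 0.7, it matches ANCOVA (both 95%).
- **The three degrees of freedom assume four time levels.** The article's wording lists three, and P300, with two recordings, has one.
- **Completers.** A reader might infer that the analysed set shrinks to completers, since repeated-measures ANOVA uses only complete records. But multiple imputation is planned, and the expected 10% dropout (about 6 of 56) plausibly counts as a small number. What remains is that this number is undefined and nothing is said for larger losses.
- **Stopping stimulation.** The Discontinuation section says: "Participants discontinued from the intervention will continue to receive standard clinical care, and their safety will be monitored until symptoms resolve or stabilize". A reader might infer that outcome ratings end there. The section does not say so, and Study design schedules assessments at every visit without that exception. Silence in a condensed article does not support the inference.

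Repeated-measures ANOVA is a legitimate choice in a trial described as exploratory. What does not fall away is the stated rule itself, which is less efficient than a direct adjusted comparison in every setting run.

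**Conclusion.** The point holds for the continuous scales. As written, the route to a T1 group difference passes through an interaction gate and then ignores baseline. At ρ = 0.5 it has about 8% power where ANCOVA has 33% (d = 0.38), or 60% where ANCOVA has 85% (d = 0.76). The direction held throughout the range examined. The size depends on the visit correlation and on how the effect persists, and the article states neither.

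Baseline adjustment is not a rescue: at d = 0.38 power stays between 28% and 45% with 25 per arm. For response, the defect is one of wording. "Each outcome" is too broad, and one analysis must be named as primary. The condition on imputation should go, because whether the number missing is small would be judged after the data are seen.

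**What to change.** - **HAMD-17 and BDI-II:** a mixed model on T1, T2 and T3 with baseline score as covariate and group-by-visit terms, testing the T1 contrast directly with no interaction gate. SPSS MIXED can fit this.
- **P300:** ANCOVA on the T1 value with baseline as covariate, following the two recordings in Table 1. Study design lists P300 among assessments at all four visits, so the two should be aligned.
- **"Each outcome":** limit to continuous outcomes. C-SSRS, with ordinal ideation ratings and categorical behaviour events, needs its own named analysis.
- **Response at T1:** name one analysis as primary, either chi-square/Fisher as planned or logistic regression adjusted for baseline HAMD-17. The second is an option, not a correction.
- **Missing data:** apply the planned multiple imputation to response in all randomized patients, whatever the amount missing.

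The cost is revised wording and slightly more analysis work, with the same software and no new data.

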### Analysis of EEG

#### Data preprocessing (using EEGLAB software)

EEG preprocessing will be performed using the EEGLAB toolbox in MATLAB, comprising filtering, artifact removal, epoching, baseline correction, and event-related potential (ERP) averaging (38). Continuous data will first be band-pass filtered (0.1–0.5 Hz high-pass; 30–40 Hz low-pass) to attenuate slow drifts, electromyographic noise, and line interference. Independent Component Analysis will then be applied to remove ocular and myogenic artifacts, with components identified based on spatial topography and time-frequency characteristics. Data will subsequently be segmented into stimulus-locked epochs and baseline-corrected using a pre-stimulus interval to minimize low-frequency fluctuations. Artifact-free epochs for target and standard tones will be averaged separately to enhance event-related activity and suppress background EEG. Finally, the P300 component will be identified as the most positive peak within the 300–600 ms post-stimulus window at the Cz electrode, with both baseline-to-peak amplitude and peak latency quantified for subsequent statistical modeling.

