### Randomization and allocation concealment procedure

Computer-generated random allocation sequence (1:1 ratio) will be created using statistical software (SAS) by an independent individual who is not involved in participant recruitment, thereby ensuring that investigators cannot access or influence the original sequence. Allocation concealment will be implemented using opaque, sealed kraft paper envelopes that prevent visualization of contents under light. Each envelope will be labeled with a unique participant number corresponding to the randomization sequence but will not contain any indication of group assignment on the exterior. The printed group assignment will be folded, placed inside the appropriately numbered envelope, and sealed. An additional transparent outer sleeve (marked as “Unopened”) will be applied over the envelope, ensuring integrity through double sealing. Once a participant meets all eligibility criteria and signs the informed consent form, the researcher will provide the participant’s basic information to the coordinator and request the corresponding sequentially numbered envelope. After verifying the information, the coordinator will take out the corresponding envelope in numerical order. The envelope will be opened on-site by the researcher, and the intervention will be implemented according to the grouping information inside. After opening, the date, time, and signature of the person who opened the envelope must be marked on the envelope, which will then be archived for documentation.

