### Blinding

This study employs a single−blind design, in which participants will remain blinded to their treatment allocation (active or sham stimulation), while investigators administering the interventions and assessing outcomes will not be blinded due to the technical requirements of transcranial magnetic stimulation (TMS). Blinding of participants is critical to minimize expectancy effects and subjective reporting biases. Unblinding will be permitted only in cases of serious adverse events where knowledge of treatment allocation is required for clinical management. In all other circumstances, the blinding will be maintained until database lock and completion of the primary analysis.

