#### Secondary clinical outcomes

The C-SSRS is a clinician-administered measure used to evaluate suicide risk by assessing both suicidal ideation and suicidal behavior. Suicidal ideation is rated on a five-level severity scale (1–5), with higher ratings reflecting more severe and imminent risk. Suicidal behavior is documented as categorical events, including preparatory actions, aborted or interrupted attempts, and actual suicide attempts. The C-SSRS has demonstrated strong reliability, validity, and predictive value in clinical populations and is widely adopted as a primary outcome measure in suicide-focused research (33).

The BDI-II is a 21-item self-report measure assessing the core symptom domains of depression. Each item is rated on a 4-point scale (0–3), yielding a total score ranging from 0 to 63, with higher scores indicating more severe depressive symptoms. The BDI-II has demonstrated excellent internal consistency (Cronbach’s α ≈ 0.94) and robust psychometric validity, supporting its use as a reliable indicator of depressive symptom severity in clinical research (34).

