### Confidentiality

Participating investigators and their research staff will strictly maintain participant confidentiality and privacy. Accordingly, all study-related documents, data, and other generated materials will be treated with strict confidentiality. No study-related information or data will be disclosed to unauthorized third parties without prior written approval. All study procedures will be conducted in environments ensuring maximum privacy protection. Potential participants will be offered the opportunity to discuss study involvement without parents or guardians present.

All participant information will be managed in compliance with institutional and regulatory data protection standards. Personally identifiable data will be replaced with unique study identification codes, with access to the encryption key restricted to authorized research personnel. Electronic data will be stored on password-protected systems, and physical records will be secured in locked cabinets within controlled-access research facilities. No identifiable information will appear in any reports, presentations, or publications.

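### Offline P300 preprocessing is not masked to arm or visit: the reason given for unblinded outcome assessment does not apply to stored EEG files, and several preprocessing choices have no objective criterion

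*Protocol article*

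**What the plan says.** The Blinding section describes a single-blind trial in which participants are masked but "investigators administering the interventions and assessing outcomes will not be blinded due to the technical requirements of transcranial magnetic stimulation". It makes no separate arrangement for EEG. P300 appears among the secondary outcomes in the Abstract and among the outcome measures under Study design.

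The preprocessing section filters the continuous data ("band-pass filtered (0.1–0.5 Hz high-pass; 30–40 Hz low-pass"), applies independent component analysis to remove ocular and muscle artifacts "with components identified based on spatial topography and time-frequency characteristics", cuts and baseline-corrects epochs, and averages the artifact-free ones. Scoring then follows a stated rule: "the P300 component will be identified as the most positive peak within the 300–600 ms post-stimulus window at the Cz electrode".

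Two other sections touch on coding. Under Confidentiality, "Personally identifiable data will be replaced with unique study identification codes". Under Randomization and allocation concealment, "Each envelope will be labeled with a unique participant number corresponding to the randomization sequence", and the researcher opens the envelope. Neither says that arm or visit is hidden from whoever processes the EEG.

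**The concern.** The operator of a tilted-coil sham has to know the allocation. A person cleaning a stored recording does not. The article gives one technical reason for leaving outcome assessment open and applies it to outcomes in general, including one for which the reason has no force.

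This matters because of what P300 is meant to contribute. HAMD-17, C-SSRS and TESS are scored by staff who are not blinded (for the C-SSRS: "The C-SSRS is a clinician-administered measure used to evaluate suicide risk"), and BDI-II is self-reported. P300 is the only outcome taken from an instrument. The Introduction looks to it for objective biomarkers, and the Discussion counts it among the trial's strengths. If the person preparing the waveforms can know which files are active and which are post-treatment, part of that objectivity is lost for no practical reason.

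**Working it through.** No figure in the plan needs reproducing here. The check sets the sections side by side.

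**1. Does the plan leave EEG processing unmasked?** The Blinding section unblinds those who assess outcomes, P300 is an outcome, and no section makes an exception. The study codes under Confidentiality protect identity. The envelope number follows the randomization sequence and the envelope is opened by the researcher, so that number does not hide arm from study staff. The blinding integrity check and sensitivity analyses promised in the Discussion address how far blinding is compromised by the tilted-coil sham, not EEG handling.

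**2. Where is there latitude?**

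| Step | Rule in the article | Open to choice? |
|---|---|---|
| Filter | Ranges: 0.1–0.5 Hz and 30–40 Hz | Yes, until one setting is fixed |
| Component removal | Topography and time-frequency features | Yes; no threshold, classifier or second reader named |
| Epoch selection | Artifact-free | Yes; no criterion stated |
| Peak scoring | Most positive peak, 300–600 ms, Cz | No |

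Discretion is confined to preprocessing, but the fixed peak rule is applied to a waveform those steps have already shaped.

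**3. How much can one epoch matter?** The inputs are a task of about 3 minutes (180 s), 20% targets, an inter-stimulus interval of 1.0–1.5 s (midpoint 1.25 s) and tones of 50–100 ms.

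- Interval read as onset to onset: 180 / 1.25 × 0.20 = 28.8 targets.
- Interval read as offset to onset, 100 ms tones: 180 / 1.35 × 0.20 = 26.7 targets.

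So there are about 27–29 target epochs per recording before any rejection, and each one discarded is 1/29 to 1/27, or 3.4–3.7% of the average. This shows that epoch choices are not negligible. It does not give a bias.

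**4. What would reach the planned test?** The analysis section applies repeated-measures ANOVA, group by time, to each outcome. I take this to include P300, since no other model is named for it. Table 1 schedules P300 at baseline (T0) and day 10 (T1). Let b be the mean shift that processing adds in each cell. The bias in the interaction contrast is

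(b active,T1 − b active,T0) − (b sham,T1 − b sham,T0).

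- Same shift at both visits within an arm: each bracket is 0, so the bias is 0.
- Same shift in both arms at a visit: the brackets are equal, so the bias is 0.
- Shift differing by arm and visit together, for example only in active T1 files: the bias equals that shift.

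The last pattern requires the processor to know or infer both arm and visit, which is what masking would prevent. The article gives no P300 standard deviation and nothing from which to estimate b, so the contrast cannot be evaluated numerically.

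**The case against.** The strongest reply is that this is a condensed article. Who processes EEG files, and under what codes, may be set out in a fuller protocol or EEG procedure, and the Blinding section speaks of investigators without naming an offline processor. That has some force: reading the section as covering EEG processing is an inference. But the section makes a positive statement about outcome assessment and gives a reason for it. A reader following the article as written would find nothing that keeps arm or visit from the EEG processor.

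Several stronger readings are tempting, and the document does not support them.

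- A reader might infer that P300 scoring as a whole is a matter of judgement. It is not: electrode, window and peak rule are fixed. The article also does not say that components are picked by hand; a classifier could use the same features.
- A reader might infer that the filter is tuned recording by recording. The article gives ranges but does not say the setting varies between files, and one setting applied to all could not be steered by arm.
- A reader might infer that P300 is the only outcome that could be free of an unblinded rater. BDI-II is self-reported by participants who are meant to be blinded, so it already has that property. P300 is the only instrument-based outcome, which is a narrower claim.

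It is also fair to say that the Discussion calls the EEG analysis exploratory, admits possible investigator bias from the single-blind design, and nowhere claims P300 as independent confirmation of a HAMD-17 effect. Unblinded rating of HAMD-17, on which the primary outcome rests, is the more serious problem.

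**Conclusion.** The point holds in limited form. The stated reason for unblinded assessment does not extend to offline EEG work, no section masks that work, and component removal, epoch selection and filter setting lack a fixed criterion. Following the article as written therefore permits an avoidable bias in a secondary, exploratory outcome.

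Its size is unknown. A reader might attach an inflated false-positive rate by assuming a microvolt shift in one arm and a between-patient standard deviation. The document supplies neither, and a two-sample comparison of a one-arm shift is not the planned group-by-time test. The conclusion assumes that the Blinding statement covers P300, as its wording suggests, and that the ANOVA for each outcome is the P300 analysis. It is worth acting on because the remedy is cheap and still available at any time before the recordings are processed.

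**What to change.** Amend the Blinding section and the EEG preprocessing section to state that:

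1. T0 and T1 recordings are exported under random codes that hide arm and visit, by someone who does not do the processing. The independent person who creates the allocation sequence could do this, but the article does not say that person remains available at analysis. Study design says all assessments are made at all four time points; if P300 is also recorded at later visits, those files should be coded too.
2. One high-pass and one low-pass cut-off, and the criteria for rejecting components and epochs, are fixed in advance and applied to every file.
3. Preprocessing and peak scoring are completed and locked before the codes are released.
4. The numbers of components and epochs removed are logged per file and reported by arm.

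The cost is a few hours of file handling, a locked processing step and a few sentences of text. Recruitment, treatment and clinical ratings are untouched. The change removes only knowledge-driven bias in offline processing. Influence from unblinded staff during task instruction and recording remains, as does any effect of participants guessing their arm under the tilted-coil sham, and the report should say so.
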